## Background

Parkinson’s disease (PD) is a major worldwide health problem
[1], with a reported incidence rate ranging from 11 to 19/100,000 per year in the European population
[2]. Balance and walking impairments are present even in the early stages of PD
[3-6] and have been shown to be associated with restrictions in everyday activities
[7] and reduced quality of life (QoL)
[8].

Furthermore, elderly with PD have shown reduced levels of physical activity
[9] and a nine times increased risk of injurious falls, compared with the healthy elderly
[10]. As PD progresses, balance problems gradually increase and are generally non-responsive to or worsen with levodopa treatment
[11-13]. Currently, there is a growing body of research that highlights the role of physical exercise as an essential part of managing the disease, with potential neuroprotective mechanisms
[14,15]. The effects of balance training on balance and gait performance are promising for individuals with PD
[16-18], although several questions remain unanswered, particularly regarding dose, intensity and duration, as well as regarding specific exercises to improve balance control in the different stages of the disease
[17-21]. Additionally, there is a lack of knowledge of the long-term effects of training interventions on participation in everyday living, such as physical activity and QoL
[16].

Balance control relies on the interaction of several physiological systems (the musculoskeletal, neuromuscular, cognitive and sensory systems) with environmental factors and the performed task
[22]. Balance impairment or postural instability in individuals with PD is often associated with poor or absent *reactive responses* following external perturbations, such as performing a rapid step following a slip or trip
[23]. However, as degeneration of the basal ganglia affects many physiological systems essential for balance control, balance disorders in PD cannot be addressed to one single function but, rather, are the result of impairments of multiple systems
[24-26]. First of all, dysfunction of the basal ganglia influences *sensory integration*, i.e. the ability of the central nervous system to transform different modalities of sensory information (somatosensory, visual and vestibular) into a single reference frame, which is important for estimation of limb and body position in relation to the environment
[27]. Particularly, individuals with PD have shown impaired proprioception

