#### Progressive overload

Based on previous recommendations
[17] and national guidelines for physical training
[52], as well as our experience from a pilot study of balance training in PD (data not yet published) and balance training in elderly
[53], we believe that the training frequency, duration and total training dose planned for use in the proposed study (three 1-hour sessions/week during 10 weeks) will be sufficient to improve balance performance in elderly with mild to moderate PD. To achieve optimised challenges to individual capacities, the physiotherapists will individually adjust the difficulty level of the exercises for each balance component as follows:

*Sensory integration:* increased surface unevenness and restricted field of vision (vision-restricting glasses, carrying an object)

*APAs:* increased movement amplitude and velocity

*Motor agility:* increased gait complexity (e.g. altering velocity, step patterns, etc.), increased gait demands according to planned (awareness of upcoming sequences/tasks) and unplanned shifts upon verbal commands (unawareness of upcoming sequences/tasks) between different gait conditions, reciprocal movements and walking directions

*Stability limits:* changing the area or condition of the BoS and increasing leaning movement amplitude

Intermittent presence of reactive postural adjustments will be used as an indicator of the appropriate difficulty level. To target multi-task performance in PD, cognitive (e.g. counting, remembering items/numbers) and secondary motor tasks (e.g. carrying and/or manipulating objects)
[54], will be introduced in Block B and further progressed in Block C (see Table
2). Multi-task training will be individually adjusted for each participant. The level of difficulty for the secondary tasks (motor or cognitive) will be considered appropriate if the primary task is affected (e.g. decreased gait velocity or increased stride variation). Moreover, as described above, training demands will additionally be challenged by increasing variation through the course of the program.

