#### Training/intervention procedure

The balance training will be performed in groups of five to seven participants in the facilities of the Physiotherapy Clinic at Karolinska University Hospital. To secure progression and safety, all training sessions will be led by two physiotherapists with experience of working with PD and elderly patients. To standardise the intervention and secure adherence to the proposed theoretical framework, all physiotherapists will participate in a theoretical and practical workshop before the intervention starts and will be supervised during the course of the training.

Every training session will start with a warm-up session for 5 min, consisting of varied walking tasks aiming to boost the cardiovascular system. The following 50 min (short rests included) will focus on highly challenging exercise blocks (approximately 10 min per block) of standing and walking conditions. The balance components of stability limits and APAs will mainly be addressed through standing exercises, and the balance components of motor agility and sensory integration will mainly be addressed in walking exercise conditions.

The program will end with a 5-min cool-down session with slow walking, axial stretching and breathing exercises. The number of exercise blocks for each training occasion and the distribution between standing and walking exercises will be adjusted to the level of ability in each group. After each training occasion, individuals’ performance of the exercises included will be briefly documented, as an evaluation of both the appropriateness of exercises and the current level of difficulty. Adverse events (defined as an injury or medical event that restricts everyday activities and participation in the intervention) and training adherence will be monitored and recorded
[58].

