### Control group

The subjects in the control group will receive usual care from their medical practitioner and/or the community services, and will not be restricted in participating in ongoing rehabilitation programs. The control group will be offered the same balance program after study termination.

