		**ICF**		
**Instruments**	**Domains**	Body functions	Activity	Participation
*Laboratory tests*				
- Electronic walkway^*^	Temporal and spatial gait parameters during single/multi-tasking conditions	X	X	
- Mod-CTSIB	Sensory integration	X		
*Clinical tests*				
- Mini-BESTest	Subdomains of balance performance	X	X	
- One-leg stance test	Balance performance, standing on one leg		X	
- Modified figure of eight test	Balance performance, walking in a figure of eight with reduced BoS		X	
*Free-living assessment*				
- Accelerometer	Physical activity		X	
*Questionnaires*				
- FES-I	Fear of falling		X	
- UPDRS ADL	Activities of daily living		X	
- SF-36	Generic health-related QoL			X
- PDQ-39	PD-specific health-related QoL			X

^***^GAITRite, CIR Systems Inc., Clifton, NJ, USA.

BoS = base of support; PD = Parkinson’s disease; QoL = quality of life.

FES-I = Fall Efficacy Scale International; Mini-BESTest *=* Mini Balance Evaluation Systems Test; Mod-CTSIB = Modified Clinical Test of Sensory Interaction and Balance; PDQ-39 = Parkinson’s Disease Questionnaire; SF-36 = 36-item Short-Form Health Survey; UPDRS ADL = the activities of daily living (ADL) section of the Unified. Parkinson’s Disease Rating Scale, part II.

Participants in both the intervention and the control group will be tested prior to and after the 10-week intervention, and at 9 and 15 months’ follow-up after entering the study. All physical measurements will be conducted during the ON phase of their levodopa medication and at the same time of day to restrict the influence of medication fluctuations. The order of the physical tests (laboratory and clinical, as described below) will be randomised for each participant to avoid systematic bias.

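### The adverse event definition requires restricted participation in the intervention, so no control event can qualify and harms cannot be compared with usual care

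*Protocol article*

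**What the plan says.** The definition is in the protocol article under Training/intervention procedure: "Adverse events (defined as an injury or medical event that restricts everyday activities and participation in the intervention". The same sentence adds "and training adherence will be monitored and recorded". No other section defines adverse events, and Table 3 lists no falls or injury outcome.

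Four other statements determine how the definition works:

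- Control group: "The subjects in the control group will receive usual care from their medical practitioner and/or the community services", and "The control group will be offered the same balance program after study termination".
- Progressive overload gives the training as "three 1-hour sessions/week during 10 weeks".
- Outcome measures and test procedure has both arms "tested prior to and after the 10-week intervention, and at 9 and 15 months’ follow-up after entering the study".
- Exercise on prescription, placed under the intervention group, adds a group meeting and a Physical Activity on Prescription after the last session.

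Two statements bear on why harms matter here. The Background describes people with this disease as having "a nine times increased risk of injurious falls, compared with the healthy elderly". The main part of each session "will focus on highly challenging exercise blocks (approximately 10 min per block) of standing and walking conditions".

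**The concern.** An event must do two things to count: restrict everyday activities, and restrict participation in the intervention. The second condition depends on being allocated to training, so the definition of a harm differs by arm. A control who falls and is confined to the home for weeks has no adverse event under this wording. A trained participant with the same injury has one if it also restricts training.

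The programme deliberately challenges stability, in people whom the article describes as at raised risk of injurious falls. Injuries are therefore expected to some degree whether or not anyone trains. A training-arm count is interpretable only beside a usual-care count obtained with the same rule. Without one, the trial cannot inform the injury side of a decision to adopt the programme in outpatient care, which the abstract names as the goal if it is effective. The loss runs both ways, since a protective effect on injuries could not be seen either.

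**Working it through.** The article gives no figure for harms, so there is none to reproduce. The check applies the definition to each arm and period and then sizes the observation time in which an event could count.

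**Applying the two conditions**

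- *Controls, entry to 15 months.* The first condition can be met. The second cannot, because the programme is offered only after study termination. No event qualifies.
- *Trained arm, weeks 1 to 10.* Both conditions can be met. An event that limits daily life but leaves training participation unrestricted does not qualify.
- *Trained arm, after week 10.* The sessions have ended. The second condition can be met only if the activity prescription counts as the intervention, which the article does not settle.

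**Is the *and* loose wording for *or*?** The authors write *and/or* when they mean it. It appears under Progressive overload, on secondary motor tasks, and in the first sentence of Control group quoted above. The definition has a plain *and*, so the literal reading is the natural one.

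**Size of the window**

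Inputs: 40 per group and 15% dropout (Sample size); 10 weeks of training; follow-up to 15 months after entry.

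- Person-years per arm with complete follow-up: 40 × 15/12 = 50.
- If the full 15% were lost at entry: 40 × 0.85 = 34 participants, and 34 × 15/12 = 42.5. The plausible range is about 42.5 to 50.
- Training exposure with complete follow-up: 40 × 10/52 = 7.7 person-years. With 34 participants: 34 × 10/52 = 6.5.
- Share of the trained arm's follow-up: 15 months is 15 × 52/12 = 65 weeks, and 10/65 = 15%.

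| | Follow-up (person-years) | Time in which an event can count |
|---|---|---|
| Control | 42.5 to 50 | 0 |
| Trained, sessions only | 42.5 to 50 | 6.5 to 7.7 |
| Trained, prescription counted as intervention | 42.5 to 50 | up to the whole follow-up |

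The control entry is 0 under any injury rate. The number of missed events cannot be derived, because the Background figure is a relative risk and the article gives no absolute rate.

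**The case against.** The best defence is that the sentence was never meant to support a comparison. It sits beside session-by-session documentation and training adherence, and reads as tolerability monitoring of the sessions. The aim is efficacy, and no harms outcome or between-arm harms test is planned. A condensed article may also leave the collection of events in controls, and after training, to a fuller document. Finally, the phrase could be meant as a list of two areas an event may affect, so that either would suffice.

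Part of this stands. Silence about collection procedures is not the point here, and a fuller document may say more. If *or* was intended, events in controls and during follow-up could qualify. But the text says *and*, and the definition is stated rather than left open. A definition suited only to tolerability of the sessions still leaves the trial without comparable harms data.

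Some stronger readings are tempting, and the article does not support them:

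- *The trial will report a spurious excess of harms.* For illustration, 6 of 40 against a definitional 0 of 40 gives a two-sided Fisher p of 0.026, and 5 of 40 gives 0.055. The plan sets out no such test, so this is not a forecast of its results.
- *Only injuries that stop attendance are counted.* The word used concerns restriction. Someone who attends but has to omit or modify exercises could qualify.
- *Nothing at all can count after week 10.* This holds for controls. For the trained arm it depends on the status of the activity prescription.
- *Control injuries will be common.* A relative risk against healthy elderly people does not establish that.

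**Conclusion.** The point holds for the definition as written. Control events are excluded by construction for the whole study. Trained-arm events are under-counted during training and, if the intervention means the sessions, excluded for the remaining 85% or so of follow-up. The harms record therefore cannot show whether the training raises or lowers injuries relative to usual care.

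This rests on two assumptions: that *and* means both conditions are required, which the authors' usage elsewhere supports, and that usual care is not itself an intervention in the sense of the definition, which the article's use of the term supports. The exact trained-arm share also depends on how the activity prescription is classed; the control-arm conclusion does not.

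The consequence is confined to harms. The primary outcomes, sample size and efficacy analyses are untouched. The change should be made because it is cheap and the present wording forecloses the comparison, but it does not threaten the trial's main conclusions.

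**What to change.** Define an adverse event by the first condition alone, an injury or medical event that restricts everyday activities, and remove participation in the intervention from the definition. Then:

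- ask the same question in both arms at the 10-week, 9-month and 15-month visits already planned, each covering the period since the last visit;
- keep restricted participation in training as a separate flag for the trained arm, so that the tolerability information is retained;
- report counts descriptively by arm, without a formal test.

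The cost is one reworded definition and one added question at existing visits. Reported counts will be higher than under the present wording. With 40 per group and no sizing for harms, precision will be low, so the counts should be presented as descriptive.

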#### Exercise on prescription

We predict that increased physical functioning following training will lead to greater confidence in everyday participation and therefore an increased level of physical activity. However, targeted advice is needed for long-term behavioural change
[59,60]. Therefore, a meeting will take place after the last training session, where the participants will participate in a group discussion, led by physiotherapists, on how to sustain or increase their level of physical activity. Participants will be given Physical Activity on Prescription (PaP)
[59,60], together with a leaflet on benefits of physical activity and health in PD.

### Control group

The subjects in the control group will receive usual care from their medical practitioner and/or the community services, and will not be restricted in participating in ongoing rehabilitation programs. The control group will be offered the same balance program after study termination.

### Outcome measures and test procedure

According to the wide disability spectrum associated with balance impairments in PD
[16,61], a multi-dimensional battery of outcomes will be used to identify potential training effects. As illustrated in Table
3, we have applied the International Classification of Functioning, Disability and Health (ICF) as a conceptual framework to target relevant constructs of *body functions* (i.e. physiological functions of body systems), *activity* (i.e. execution of a task or action by an individual) and *participation* (i.e. involvement in a life situation)
[62]. As previously suggested by Dibble et al.
[16], our outcome measures represent a wide spectrum within the concepts of disability and health, from laboratory measurement of balance and gait performance, to free-living assessment of physical activity and self-perceived domains of QoL and participation in everyday living (see Table
3). Primary outcome measures will be functional balance performance, change in gait velocity (m/s) between single and dual task walking, and fear of falling. 

**Table 3 T3:** **Classification of outcome measures****using the International Classification****of Functioning, Disability and****Health (ICF)**

		**ICF**		
**Instruments**	**Domains**	Body functions	Activity	Participation
*Laboratory tests*				
- Electronic walkway^*^	Temporal and spatial gait parameters during single/multi-tasking conditions	X	X	
- Mod-CTSIB	Sensory integration	X		
*Clinical tests*				
- Mini-BESTest	Subdomains of balance performance	X	X	
- One-leg stance test	Balance performance, standing on one leg		X	
- Modified figure of eight test	Balance performance, walking in a figure of eight with reduced BoS		X	
*Free-living assessment*				
- Accelerometer	Physical activity		X	
*Questionnaires*				
- FES-I	Fear of falling		X	
- UPDRS ADL	Activities of daily living		X	
- SF-36	Generic health-related QoL			X
- PDQ-39	PD-specific health-related QoL			X

^***^GAITRite, CIR Systems Inc., Clifton, NJ, USA.

BoS = base of support; PD = Parkinson’s disease; QoL = quality of life.

FES-I = Fall Efficacy Scale International; Mini-BESTest *=* Mini Balance Evaluation Systems Test; Mod-CTSIB = Modified Clinical Test of Sensory Interaction and Balance; PDQ-39 = Parkinson’s Disease Questionnaire; SF-36 = 36-item Short-Form Health Survey; UPDRS ADL = the activities of daily living (ADL) section of the Unified. Parkinson’s Disease Rating Scale, part II.

Participants in both the intervention and the control group will be tested prior to and after the 10-week intervention, and at 9 and 15 months’ follow-up after entering the study. All physical measurements will be conducted during the ON phase of their levodopa medication and at the same time of day to restrict the influence of medication fluctuations. The order of the physical tests (laboratory and clinical, as described below) will be randomised for each participant to avoid systematic bias.

#### Laboratory tests

*Temporal and spatial gait**parameters* will be measured using a 9 m electronic walkway (GAITRite, CIR Systems Inc., Clifton, NJ, USA) sensing the geometry of each step through embedded pressure sensors. Four types of gait conditions will be evaluated during (i) self-selected and (ii) fast speed, (iii) while performing a cognitive (reciting every second letter of the alphabet) and (iv) a motor dual-task (carrying a tray with a glass of water). Spatial and temporal gait parameters will be analysed, as will variability and asymmetry in gait performance.

The *Modified Clinical Test of**Sensory Interaction and Balance* (Mod-CTSIB) will be used to measure sensory integration during static standing
[63]. To discriminate between the sensory systems (somatosensory, visual and vestibular), participants will be timed while standing on a force plate (50 cm x 50 cm; Kistler, Winterthur, Switzerland) in four different sensory conditions: (i) standing on a firm surface with the eyes open; (ii) standing on a firm surface with the eyes closed; (iii) standing on a compliant surface with the eyes open; and (iv) standing on a compliant surface with the eyes closed. Outcomes will be the time able to stand (max 30 s) and postural sway in the anterior-posterior and medio-lateral direction.

#### Clinical tests

The *Mini Balance Evaluation Systems**Test* (Mini-BESTest) will be used to assess underlying subsystems of balance performance (APAs, postural reactive responses, sensory integration and dynamic gait)
[64].

The *One-leg stance test* will be performed with the subject standing on one leg as long as they are able to
[65]. This test requires appropriate APAs for CoM transition from a standing position to a restricted BoS.

The *Modified figure of eight**test* will be used to evaluate dynamic balance during walking
[66]. The subject is instructed to walk in a figure of eight (marked with 40 mm-wide tape on the floor, each loop having an internal diameter of 1.63 m) as fast as possible, with every step touching the tape
[66].

#### Free-living assessment

*Physical activity* in everyday life will be assessed with accelerometers (Actigraph GT3X+, Manufacturing Technology Inc., Fort Walton Beach, FL, USA). The accelerometer will be used under free-living conditions, worn around the waist, using an elasticized belt, for 7 consecutive days. Outcomes will be total physical activity, expressed as counts per minute and steps per day, and time spent on different intensity levels as well as time spent sedentary
[67].

#### Questionnaires

The Activities of Daily Living section of the *Unified Parkinson’s Disease Rating**Scale (UPDRS ADL)*, part II, will be used to measure activities of daily living
[68].

The *Falls Efficacy Scale International-I* (FES-I) will be used to measure participants concern of fear of falling during a variety everyday activities (e.g. getting dressed, taking a shower, climbing stairs or going to the shop)
[69].

As previously suggested by Brown et al. (2009), assessment of *Health-related QoL* in PD should include both a generic and a PD-specific instrument
[70]. The Short Form-36 (SF-36) will be used to evaluate generic health-related QoL
[70,71] and the 39-item Parkinson’s Disease Questionnaire (PDQ-39) will be used to evaluate PD-specific health-related QoL
[70,72].

